## Abstract

**Background:**

Progress in vitrification techniques has allowed reproductive physicians to consider new strategies for using progestin as an alternative to a GnRH analogue to improve in vitro fertilisation (IVF). However, the role of progestin in blocking luteinising hormone (LH) surges and its potential in clinical practice are unclear, especially for poor responders. We designed a prospective randomised controlled trial (RCT) to compare the efficacy of a gonadotropin-releasing hormone (GnRH) antagonist and progestin in blocking LH surges and premature ovulation in poor responders.

**Methods/design:**

Poor responders who meet the Bologna criteria will be randomised to one of two stimulation regimens—gonadotropin-releasing hormone (GnRH) antagonist or progestin-primed ovarian stimulation (PPOS)—using a computer-generated random number. Fresh embryos were transferred in the GnRH antagonist group and frozen embryos were transferred in the PPOS group. The primary outcome is the incidence of premature LH surges. Secondary outcomes include the number of oocytes retrieved, the number of embryos available for transfer, implantation rates and clinical pregnancy. The sample size for this trial is estimated as 340 participants, with 170 participants in each group. The data analysis will be by intention to treat.

**Discussion:**

To our knowledge, this is the first RCT to examine the efficacy of administering progestin orally to block LH surges and premature ovulation compared with the GnRH antagonist protocols in poor responders undergoing IVF treatment.

**Trial registration:**

www.chictr.org.cn. ChiCTR-IPR-17010906. Registered on 18 March 2017.

**Electronic supplementary material:**

The online version of this article (10.1186/s13063-018-2850-x) contains supplementary material, which is available to authorized users.

## Background

Gonadotropin-releasing hormone (GnRH) antagonists have been used to suppress pituitary activity and to prevent premature surges of luteinising hormone (LH) during controlled ovarian stimulation since the 1990s [1]. GnRH antagonist therapy does not produce a flare effect and rapidly suppresses gonadotropins and it can be initiated in the late follicular phase of the menstrual cycle. Thus, GnRH antagonists are considered to be beneficial for poor responders since there is less suppression in the early follicular phase [2]. Previous studies of poor responders have shown that a GnRH antagonist protocol is associated with decreased cycle cancellation and fewer days of gonadotropin stimulation, but the clinical pregnancy outcomes were not significantly different between GnRH antagonist and agonist protocols [3].

Progress in vitrification techniques has allowed reproductive physicians to consider new strategies for using progestin as an alternative to a GnRH analogue for improving in vitro fertilisation (IVF) [4–8]. Progestin can inhibit the pre-ovulatory LH surge when it is administered during the early part of the cycle before oestrogen priming [9–11]. Progestin also alters pituitary responsiveness to GnRH and gonadotrophin secretion [12, 13]. For more than 50 years, progestin has been widely applied to control ovulation in hormonal contraception [14], and since 2014, its use has been extended to preventing premature ovulation in IVF [5, 6]. Our recent studies demonstrated that progestin-primed ovarian stimulation (PPOS) produced a gradually decreasing LH level during ovarian stimulation, with a low incidence of LH surges (0.15%) in women with a normal ovarian reserve [6]. PPOS also produces an acceptable pregnancy outcome compared with the conventional short protocol [4–8]. However, currently, there are no data comparing the efficacy and safety of a GnRH antagonist and progestin in blocking LH surges and premature ovulation in poor responders.

GnRH antagonists have a reported failure rate of approximately 0.34–8.0% for controlling premature LH surges in women with a normal ovarian reserve [1–3]. An antagonist failure is more likely to occur in women with advanced age, a diminished ovarian reserve and poor response to gonadotropins [15]. Our prospective trial in a population of poor responders showed that ovulation of the dominant follicle was controlled well using progestin administered orally as a surrogate for a GnRH antagonist, with low incidence rates of LH surges and premature ovulation (3.0%) [8]. Moreover, progestin priming prolonged the follicular phase by one more day, and the diameter of the pre-ovulatory follicle was larger than those of natural cycle patients. These data indicated that progestin treatment significantly suppressed follicular rupture and provided a wide window for oocyte retrieval [8]. Therefore, we assumed that progestin may show some superiority in controlling premature LH surges compared with GnRH antagonists in poor responders. Thus, we have developed this well-designed large-sample prospective trial to investigate the potential of progestin for poor responders undergoing IVF treatment.

## Methods/design

In this trial, the efficacies of a GnRH antagonist and progestin are being compared in 340 poor responders undergoing IVF through intracytoplasmic sperm injection (ICSI). The participants will be enrolled in Shanghai Ninth People’s Hospital affiliated with Shanghai Jiaotong University School of Medicine. The study has been approved by the Institutional Review Board of Shanghai Ninth People’s Hospital (2016–198-T142). Informed consent will be obtained from each patient before any study procedure is performed, in accordance with good clinical practice.

This protocol has been written in accordance with the Standard Protocol Items: Recommendations for Interventional Trials (SPIRIT). A SPIRIT checklist is provided in Additional file 1. Any significant modifications to the protocol will require a formal protocol amendment, agreed by the project team and approved by our Institutional Review Board. Minor administrative changes to the protocol will be documented in a memorandum. The study flowchart is shown in Fig. 1.

**Fig. 1 Fig1:**
[figure not shown]
Flowchart of this randomised controlled trial comparing PPOS with a GnRH antagonist in poor responders. ET embryo transfer, FET frozen-thawed embryo transfer, GnRH gonadotrophin-releasing hormone, ITT intention to treat, LH luteinising hormone, PPOS progestin-primed ovarian stimulation

### Participants

#### Inclusion criteria

The following are the inclusion criteria:Women who have a history of infertility ≥1 yearWomen aged >22 and <42 yearsWomen with spontaneous menstrual cycles of 21–35 daysWomen who have at least one of the following indications for IVF or ICSI: tubal factor, male factor, diminished ovarian reserve, endometriosis or unexplained factorsWomen diagnosed as poor responders according to the Bologna criteria, including at least two of the three following criteria:Advanced age (≥40 years) or any other risk factor for poor ovarian responseA previous poor response with no more than three oocytes retrieved using the conventional stimulation protocolsAbnormal ovarian reserve test results, including bilateral antral follicle counts <7 or serum anti-Müllerian hormone <1.1 ng/ml

#### Exclusion criteria

Women who met any of the following criteria are excluded:Clinically significant systemic diseases, such as renal failure and systemic lupus erythematosusPremature ovarian insufficiencyUp to five previous unsuccessful IVF attemptsKnown Müllerian anomaliesAny contraindications to ovarian stimulation treatmentsUnable to comply with the study procedures

### Randomisation

Participants will be allocated randomly into one of the two arms at a ratio of 1:1 on menstrual cycle day 3. The allocation sequence will be generated utilising computer-generated random numbers. Both investigators and participants will be aware of the allocation after ovarian stimulation. The doctors and embryologists involved in oocyte retrieval and embryo transfer are blinded to the group assignments of the participants in the trial.

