### In vitro fertilisation and embryo culture

All follicles more than 10 mm will be retrieved. Follicles are flushed three times at most if no cumulus oocyte complex is present. Standard insemination or ICSI is performed within 6 h of retrieval. Embryos are examined for the number and regularity of blastomeres and the degree of embryonic fragmentation on the third day. If available, two top-quality embryos (including grade I and grade II, eight-cell blastomere embryos) in the GnRH antagonist group are transferred on the third day. The remaining top-quality embryos are frozen by vitrification, while the non-top-quality embryos are cultured for an extended time. Only blastocysts with good morphology are frozen on day 5 or 6. All top-quality cleavage embryos and the cryopreserved blastocysts are recorded as viable embryos. In the PPOS group, all top-quality embryos are frozen on the third day, while the non-top-quality embryos are cultured for an extended time and cryopreserved according to the same criteria as above.

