#### Secondary outcomes

Secondary efficacy parameters include the number of oocytes retrieved, the number of viable embryos, the clinical pregnancy rate, the implantation rate, the ongoing pregnancy rate and the cumulative live birth rates from a single IVF cycle. Clinical pregnancy will be defined as the presence of an intrauterine gestation sac at 7 weeks of gestation. Ongoing pregnancy will be defined as a viable pregnancy at 12 weeks of gestation.

The safety endpoints include the incidence rates of ovarian hyperstimulation syndrome, miscarriage, ectopic pregnancy, pregnancy complication, congenital anomalies and neonatal complications.

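### The blinding stated for embryo transfer cannot hold for fresh transfers, which by rule occur only in the GnRH antagonist arm

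*Protocol article*

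**What the plan says.** The Randomisation section of the protocol article makes two statements about who knows the allocation. One concerns the clinical side: "Both investigators and participants will be aware of the allocation after ovarian stimulation". The other claims masking for the staff at two procedures: "The doctors and embryologists involved in oocyte retrieval and embryo transfer are blinded to the group assignments of the participants in the trial".

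The section on in vitro fertilisation and embryo culture then sets a different day-3 action for each arm. If available, two top-quality embryos "in the GnRH antagonist group are transferred on the third day". For the other arm: "In the PPOS group, all top-quality embryos are frozen on the third day". The Abstract says the same in short: "Fresh embryos were transferred in the GnRH antagonist group and frozen embryos were transferred in the PPOS group".

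Embryos that are not top quality stay in culture in both arms, under the same freezing criterion: "Only blastocysts with good morphology are frozen on day 5 or 6". The count that results is defined as follows: "All top-quality cleavage embryos and the cryopreserved blastocysts are recorded as viable embryos". It is an efficacy outcome under Secondary outcomes: "Secondary efficacy parameters include the number of oocytes retrieved, the number of viable embryos".

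**The concern.** The blinding statement covers embryo transfer, yet the type of transfer is part of the allocated strategy. A person cannot be masked to the arm while carrying out a step that only one arm receives.

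Two things are at stake. First, the trial report may carry forward a description of blinded embryo transfer that the design does not allow, and readers would rely on it when judging bias in the secondary outcomes. Second, the arm-specific step on day 3 comes before a judgement that enters an outcome. Selecting blastocysts by morphology is a graded decision by laboratory staff. If those staff already know the arm, that part of the viable-embryo count is open to assessment bias.

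**Working it through.** There is no figure in the plan to reproduce, and no arithmetic applies. The check sets the blinding statement against the order of the steps and asks at each one whether the arm can be hidden.

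1. **Trigger day (primary outcome).** The outcome is a serum LH above 15 mIU/ml, a laboratory value measured before retrieval and before any embryo is handled. The blinding question at transfer does not reach it.
2. **Oocyte retrieval.** Both protocols use the same dual trigger at the same follicle size, with retrieval 36 h later. Nothing in the procedure reveals the arm, so the stated blinding is feasible here and the oocyte count is not in question.
3. **Day-3 grading.** The grading criteria do not depend on the arm. Masking is feasible if the grade is recorded before the laboratory learns whether to transfer or freeze.
4. **Day-3 action.** This step depends on the arm. A fresh transfer implies the antagonist arm, because the PPOS arm has none. Freezing all top-quality embryos with no transfer is the PPOS rule. Withholding the group label does not help, since the instruction itself carries the allocation.
5. **Day-5 or day-6 blastocyst selection.** This follows step 4 in time and adds to the viable-embryo count.

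Whether step 5 is exposed depends on the woman's embryos on day 3:

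| Top-quality embryo on day 3 | Other embryo kept in culture | Arm shown by the day-3 action | Blastocyst decision exposed |
|---|---|---|---|
| Yes | Yes | Yes | Possibly, unless the grader is separate and masked |
| Yes | No | Yes | No, nothing left to grade |
| No | Yes | No | Not by this step |
| No | No | No | No |

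Only the first row combines a revealed arm with a grading decision still to come. The document gives neither the share of women in that row nor any basis for estimating how far knowledge of the arm would move a grade.

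6. **Later frozen transfer.** The antagonist arm also vitrifies its surplus top-quality embryos and its good blastocysts. A frozen transfer can therefore come from either arm and does not by itself identify PPOS.

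**The case against.** The strongest reply is that the contradiction is narrow. The blinding sentence concerns staff at retrieval and transfer and makes no explicit claim about blastocyst assessment. Who grades blastocysts, and whether that person sees what was done on day 3, is laboratory detail that a condensed article can leave to the full protocol. The exposed group is also limited: a woman needs both a top-quality embryo and another still in culture, and poor responders have few embryos. The primary outcome, the oocyte count, the sample size and the treatment plan are all untouched.

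Most of this stands, and it sets the limits of the point. It does not rescue the statement for fresh transfers. That is a positive claim which the transfer rule makes untrue, and no further detail in a fuller protocol could restore it while the rule remains.

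A reader might go further and infer that all embryology in this trial was unblinded, or that every transfer reveals the arm. The document supports neither. Day-3 grading is not shown to have been unblinded, frozen transfers occur in both arms, and a masked blastocyst grader is possible although none is described. A reader might also want to put a number on the bias in the viable-embryo count. Any such number would rest wholly on assumed shares and assumed grading shifts.

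**Conclusion.** The blinding statement is wrong for fresh embryo transfers. This follows from the transfer rule alone and needs no assumption. For blastocyst selection the conclusion is weaker. In women with both a top-quality day-3 embryo and other embryos in culture, masking is not assured, and whether it was lost depends on staffing that the article does not describe. The viable-embryo count should therefore not be presented as blinded throughout.

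The effect is confined to a stated design property and to part of one secondary outcome. Its size cannot be derived from the document. The conclusion assumes that the day-3 rules are followed as written.

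**What to change.** - **Correct the blinding statement.** Limit it to oocyte retrieval and to day-3 embryo grading where the grade was recorded before the arm was released. Say that fresh transfers are not blinded, and that blastocyst selection after the day-3 action is not assured to be blinded. If a separate masked blastocyst grader was in fact used, say so instead.
- **Fix the order of entry.** For women not yet treated, lock the day-3 grade in the electronic data capture system before the transfer-or-freeze instruction is released to the laboratory.
- **Report the outcome in two parts.** Give viable embryos by arm as day-3 top-quality embryos and cryopreserved blastocysts, beside the total, so that readers can see whether any difference lies in the part where masking is least secure.

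The wording change and the two-part report need no new assessments, since the count is built from these two components, and they cover women already treated. The locked grade costs one ordered data entry per woman and helps only those still to come. Treatment, grading criteria and sample size stay as they are. What is given up is a blinding claim that the design cannot support.

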### Protocols

#### GnRH antagonist protocol

The flexible GnRH antagonist protocol is as follows: 150–225 IU of human menopausal gonadotropin (hMG) is administered daily from menstrual cycle day 3. After 5 days of injections, when the dominant follicles reach a diameter of approximately 14 mm, 0.125–0.25 mg of GnRH antagonist is administered daily up to the trigger day. For women with a low or normal body mass index (<25.0 kg/m^2^) or low LH levels before GnRH antagonist administration (<2.0 mIU/ml), 0.125 mg of antagonist is administered daily. For women with a higher body mass index (≥25.0 kg/m^2^) or LH levels ≥2.0 mIU/ml, 0.25 mg antagonist will be used daily up to the trigger day. The dose of hMG is adjusted according to the ovarian response. When the dominant follicles reach a diameter of 18 mm, the final stage of oocyte maturation is induced with 100 μg of triptorelin via subcutaneous injection and 5000 IU of human chorionic gonadotrophin (hCG) via intramuscular injection. Oocyte retrieval is performed 36 h later.

#### PPOS protocol

hMG at 150–225 IU and medroxyprogesterone acetate (MPA) at 10 mg are administered daily from cycle day 3. Five days later, the hMG dose is adjusted according to the ovarian response, while the MPA dose is kept the same up to the trigger day. When the dominant follicles reach a diameter of 18 mm, the final stage of oocyte maturation is induced with 100 μg of triptorelin via subcutaneous injection and 5000 IU of hCG via intramuscular injection. Oocyte retrieval is performed 36 h later.

### In vitro fertilisation and embryo culture

All follicles more than 10 mm will be retrieved. Follicles are flushed three times at most if no cumulus oocyte complex is present. Standard insemination or ICSI is performed within 6 h of retrieval. Embryos are examined for the number and regularity of blastomeres and the degree of embryonic fragmentation on the third day. If available, two top-quality embryos (including grade I and grade II, eight-cell blastomere embryos) in the GnRH antagonist group are transferred on the third day. The remaining top-quality embryos are frozen by vitrification, while the non-top-quality embryos are cultured for an extended time. Only blastocysts with good morphology are frozen on day 5 or 6. All top-quality cleavage embryos and the cryopreserved blastocysts are recorded as viable embryos. In the PPOS group, all top-quality embryos are frozen on the third day, while the non-top-quality embryos are cultured for an extended time and cryopreserved according to the same criteria as above.

### Endometrium preparation and frozen-thawed embryo transfer

Endometrium preparation uses either mild stimulation or hormone replacement therapy. For mild stimulation frozen-thawed embryo transfer cycles, we prescribe letrozole 2.5–5 mg for 3–5 days from cycle day 3 and then monitor follicular growth via serum hormone levels and ultrasound from cycle day 10. At times, treatment includes a low dose of hMG (75 IU/day) to stimulate follicle growth and the endometrial lining. When the diameter of the dominant follicle is >16 mm and the endometrial thickness is > 8 mm, with *E*_2_ > 150 pg/ml and progesterone <1.0 ng/ml, one of two procedures is performed, depending upon the LH level. If the serum LH level is <20 mIU/ml, 5000 IU of hCG is administered at night (21:00) to trigger ovulation, and the transfer of cleavage embryos is arranged for 5 days later. If the LH level is >20 mIU/ml, 5000 IU of hCG is injected the same afternoon, and the transfer is conducted 4 days later. The blastocyst transfer is arranged on the sixth or seventh day depending on serum hormone levels and ultrasound results. Dydrogesterone (Abbott Biologicals BV, the Netherlands) was administered orally at 40 mg/day and micronised progesterone capsules at 400 mg/day was administered vaginally for luteal support beginning on the third day after hCG injection.

For patients with a thin endometrium or where the frozen-thawed embryo transfer fails after stimulation cycles, hormone replacement therapy is recommended for endometrial preparation, specifically ethinyl oestradiol administered orally at 75 mcg/day from cycle day 3 onwards, which is commonly used for 14 days. Once the endometrial lining is >8 mm thick, Femoston (a yellow tablet) is administered twice per day (Abbott Healthcare Products BV, Weesp, the Netherlands), and 400 mg micronised progesterone capsules are administered daily via an intravaginal route. The time for thawing and transfer is determined on the third day after progesterone administration. The maximum number of transferred embryos is two per cycle. When pregnancy is achieved, the progesterone supplement is continued until 10 weeks of gestation.

### Hormonal measurement

Serum follicle-stimulating hormone (FSH), LH, oestradiol and progesterone levels are monitored during the ovarian stimulation. Hormone levels are measured via chemiluminescence (Abbott Biologicals BV, The Netherlands).

### Outcome measurements

#### Primary outcome

The primary outcome is the incidence of premature LH surges, defined as the serum LH > 15 mIU/ml on the trigger day, with or without dominant follicle rupture and increased serum progesterone. Premature ovulation is defined as dominant follicle rupture before the scheduled time. Increased progesterone alone is not defined as the presentation of an LH surge and is listed independently.

#### Secondary outcomes

Secondary efficacy parameters include the number of oocytes retrieved, the number of viable embryos, the clinical pregnancy rate, the implantation rate, the ongoing pregnancy rate and the cumulative live birth rates from a single IVF cycle. Clinical pregnancy will be defined as the presence of an intrauterine gestation sac at 7 weeks of gestation. Ongoing pregnancy will be defined as a viable pregnancy at 12 weeks of gestation.

The safety endpoints include the incidence rates of ovarian hyperstimulation syndrome, miscarriage, ectopic pregnancy, pregnancy complication, congenital anomalies and neonatal complications.

### Statistics

#### Sample size and power calculations

For the power calculation, previous studies reported that the incidence of premature LH surges in the GnRH antagonist protocol was 8.0%, and our recent data show that the incidence of premature LH surges and ovulation was 3.0% in poor responders using the PPOS protocol. Therefore, we hypothesise that the administration of MPA would decrease the incidence of premature LH surges. The superiority margin is 4.0%. A sample size of 166 in each group would yield 90% power to establish superiority at the 0.01 level of significance, and 109 in each group yield 90% power to establish superiority at 0.05 level of significance [16]. Given the abundant clinical resources in our clinic, the number of participants is set as 170 in each group in this trial.

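### 8.0% is an unlabelled assumption for poor responders, and even if it is accepted the planned test has about 53% power with 170 per group, not 90%

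*Protocol article*

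**What the plan says.** The protocol article, under Sample size and power calculations, plans on two rates. For the control arm, previous studies are said to have reported that "the incidence of premature LH surges in the GnRH antagonist protocol was 8.0" per cent, with no range and no population. For the experimental arm, "the incidence of premature LH surges and ovulation was 3.0% in poor responders using the PPOS protocol". The section adds: "The superiority margin is 4.0" per cent. It then makes two power statements. The stricter one reads: "A sample size of 166 in each group would yield 90% power to establish superiority at the 0.01 level of significance". The other, at the level that the analysis section uses, reads: "109 in each group yield 90% power to establish superiority at 0.05 level of significance". Finally, "the number of participants is set as 170 in each group in this trial".

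The Background is the only other place that gives an antagonist rate: "GnRH antagonists have a reported failure rate of approximately 0.34–8.0% for controlling premature LH surges in women with a normal ovarian reserve". It continues: "An antagonist failure is more likely to occur in women with advanced age, a diminished ovarian reserve and poor response to gonadotropins". The Discussion also holds that premature surges are harder to control in poor responders. Neither section gives an antagonist rate for them.

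Under Statistical analysis, the primary comparison is an intention-to-treat chi-square test of the difference in incidence, with significance at p < 0.05. No margin enters that test.

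**The concern.** Two things look wrong in the same paragraph.

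First, the control rate is stated more firmly than the Background allows. A value equal to the upper end of a range in normal-reserve women appears as a plain reported rate for a trial in poor responders. Moving from one population to the other may be reasonable, but it is a judgement and the reader is not told that it was made.

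Second, the stated power does not match the planned test. Detecting 8% against 3% with 90% power normally takes several hundred women per group, not 109 or 166. If the claim is wrong, a non-significant result from 340 women could be read as good evidence of no difference when the trial had only about an even chance of finding the effect it was planned on.

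**Working it through.** **Inputs.** Antagonist 8.0%, PPOS 3.0%, margin 4.0%, power 90%, levels 0.05 and 0.01, and 170 per group (all from Sample size and power calculations). Allocation 1:1 (Randomisation). Chi-square test at 0.05 (Statistical analysis). The protocol does not state sidedness. The planned test is taken as two-sided, the usual reading of a chi-square test of a difference.

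**Step 1: reproduce 109 and 166.** The unpooled variance sum is 0.08 × 0.92 + 0.03 × 0.97 = 0.0736 + 0.0291 = 0.1027. The formula n = 0.1027 × (z_alpha + z_power)² / D² was tried with different values of D and with one- and two-sided alpha.

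- D = 0.05 + 0.04 = 0.09, one-sided 0.05: 0.1027 × (1.645 + 1.282)² / 0.0081 = 108.58, rounded up to **109**.
- D = 0.09, one-sided 0.01: 0.1027 × (2.326 + 1.282)² / 0.0081 = 165.04, rounded up to **166**.

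Both figures match exactly. The other readings do not:

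| Reading | n per group, level 0.05 | n per group, level 0.01 |
|---|---|---|
| Margin added (D = 0.09), two-sided | 134 | 189 |
| No margin (8% v 3%), one-sided | 355 | 539 |
| No margin (8% v 3%), two-sided | 435 | 617 |
| Superiority by more than 4 points (D = 0.05 − 0.04 = 0.01), one-sided | 8,796 | 13,369 |

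(The no-margin rows use the pooled variance under the null hypothesis.) Adding the margin to the expected difference is a non-inferiority calculation: it sizes a trial to show that PPOS is not worse by more than 4 points. The protocol's hypothesis is that PPOS lowers the incidence.

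**Step 2: power of the planned test at 8.0% v 3.0%, 170 per group.** By normal approximation, the pooled rate is 0.055. The critical difference is 1.96 × √(2 × 0.055 × 0.945 / 170) = 0.0485. The standard error under the alternative is √(0.1027 / 170) = 0.0246. Power is Φ((0.05 − 0.0485) / 0.0246) = Φ(0.06) = 52.5%. Exact binomial enumeration of the chi-square test gives 53.1%.

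The normal-approximation figures at 170 per group show where the claimed power goes:

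- Margin added, one-sided 0.01: 91%. Margin added, one-sided 0.05: 98%.
- Margin removed, one-sided 0.05: 65%.
- Margin removed, two-sided 0.05: 53%.

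The antagonist rate is 8.0% in every line, so none of this loss comes from the choice of rate.

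**Step 3: dependence on the antagonist rate.** Exact power of the planned test, two-sided 0.05, 170 per group, PPOS 3.0%, counting significant results in favour of PPOS:

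| Antagonist rate (assumed) | Power |
|---|---|
| 4% | 6.8% |
| 6% | 26.2% |
| 8% | 53.1% |
| 10% | 76.6% |
| 12% | 90.8% |

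At 4%, significant results in either direction total 7.5%. In the other rows the two counts agree to the first decimal. Power near 90% with 170 per group needs an antagonist rate of about 12%.

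**The case against.** The strongest reply concerns the rate. A reader might infer that 8.0% is the most favourable figure available and therefore inflates the power. The documents do not support that. The range describes normal-reserve women, and the Background and Discussion both expect worse control in poor responders. On that reasoning the top of a normal-reserve range may be fair, or even low, for this trial. This part of the objection stands.

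A reader might also set the low end of the range against the 3.0% PPOS rate and conclude that the planned direction could reverse. That compares antagonist failures in normal-reserve women with PPOS failures in poor responders. The Background's PPOS figure for normal reserve is 0.15%, and against it the whole 0.34–8.0% range still favours PPOS. The reversal is not supported.

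The 3.0% counts surges and ovulation together, whereas the primary outcome is LH above 15 mIU/ml on the trigger day. That does not show the assumed effect to be too large. If 3.0% is a combined count, the surge-only rate is at most 3.0%.

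Two further points are fair. The sample-size section gives no citation with the 8.0%, so its link to the Background range is an inference from the matching number. And a condensed article need not carry a sensitivity table. Neither answers the power statement, which the article makes in full and which its own inputs and planned test do not deliver.

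**Conclusion.** The point holds in two parts.

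The 8.0% is a cross-population assumption presented as a reported rate. It should be labelled, but the documents do not show it to be wrong in either direction.

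The 90% power claim is wrong as written for the planned analysis. At the protocol's own 8.0% v 3.0%, power with 170 per group is about 53%, and 90% would need 435 per group. The cause is the margin added to the expected difference, together with a one-sided alpha. Changing the control rate alone would not repair the calculation.

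This rests on a two-sided test at 0.05. If the test were one-sided at 0.05, power would still be only about 65%. That the published figures used one-sided alpha is inferred from the exact match to both, since the protocol does not say so.

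**What to change.** In Sample size and power calculations:

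1. Say that 8.0% is an assumption for poor responders, that the cited range is 0.34–8.0% in women with a normal ovarian reserve, and that a higher rate is expected in poor responders but no figure is available.
2. Delete the 4.0% margin and both statements of 90% power (at 109 and at 166 per group).
3. In their place, state the power of the planned two-sided 0.05 chi-square test with 170 per group against a PPOS rate of 3.0%: about 7%, 26%, 53%, 77% and 91% for antagonist rates of 4%, 6%, 8%, 10% and 12%.

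The new figures must replace the 90% statements. Set beside them, they would leave the section contradicting itself. The cost is a few sentences or a five-row table, with no change to the conduct of the trial. The downside is that the stated power becomes less favourable.
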